## **9.3 Reporting SAEs**

All SAEs must be reported, regardless of whether they are related to the study drug.

If any SAE is found during the study, the investigator or site staff must complete and email the “SAE Form for Investigator Reporting to Sponsor” to the sponsor within 24 hours of learning of the event (or immediately for death cases).

Contact information of Sponsor's pharmacovigilance team:

[contact]

Email: [[contact]](mailto:[contact])

Address: [name]

- According to requirements, the sponsor or its designated agent will conduct follow-up together with clinical trial institution staff to obtain additional information and complete

[figure not shown]

reporting of the entire event;

- According to national regulations, the investigator is required to provide the Ethics Committee with suspected unexpected serious adverse reactions (SUSARs).

#### **9.4 Reporting Requirements after the End of Clinical Trial**

The investigator could report any SAE that occurs at any time after the end of study and is considered to be related/possibly related to the study drug to the Sponsor's pharmacovigilance team. Follow-up information on SAEs after database lock can also be reported to the Sponsor's pharmacovigilance team.

#### **9.5 Guideline for Supportive Therapy**

Subjects will be allowed to receive appropriate supportive measures as deemed necessary by the attending physician, including but not limited to the following:

- (1) Diarrhea: Prompt treatment and appropriate supportive care should be provided for diarrhea, including use of antidiarrheal drugs according to standard operation of the study institution. Antidiarrheal drugs cannot be taken as prophylactic drugs. Patients should be instructed to start antidiarrheal drugs when the following earliest symptoms appear:

- Shapeless or soft striped stool
- More frequent bowel movements within one day than usual or
- Abnormal high feces level

If blood or mucus is present in the stool or if diarrhea is accompanied by fever, administration of antidiarrheal drugs should be delayed. In such cases, appropriate microbiological specimens should be obtained to diagnose and exclude infectious pathogens. Patients should also be advised to drink clean fluid as far as possible to prevent dehydration.

- (2) Nausea/vomiting: Nausea and vomiting should be actively treated with antiemetics according to standard operation of the study institution. Patients should be encouraged to adhere to intake of plenty of oral fluid.
- (3) Anemia: Anemia may be treated with blood transfusion and/or erythropoietin as clinically indicated, but which should be clearly indicated and filled in the CRF as a concomitant medication. Colony stimulating factor is prohibited in Cycle 1 of this study.
- (4) Neutropenia: The neutrophil colony stimulating factors, including G-CSF, PEG-G-CSF, or GM-CSF are used in Cycle 1 of the study.
- (5) Thrombocytopenia: If clinically indicated, platelets can be transfused.
- (6) Dyspepsia, gastroesophageal reflux disease, peptic ulcer disease, or other gastric acid-related conditions: treatment may be provided after consultation with the sponsor if clinically indicated.

[figure not shown]

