| Grade 2 ( $\geq 1.0$ - $< 1.5 \times 10^9/L$ )                                                                                                                    | No dose adjustment required.                                                                                                                                                                                                                                                                                                                                                                                                                                                                                                                                                                                                              |
| Grade 3 ( $\geq 0.5$ - $< 1.0 \times 10^9/L$ )                                                                                                                    | 
 
1. Interrupt HQP1351 administration until toxicity resolves to <math>\geq 1.0 \times 10^9/L</math>.
 
2. Restart HQP1351 administration at the original dose level.
 
3. If Grade 3 toxicity recurs, interrupt HQP1351 administration until toxicity resolves to <math>\geq 1.0 \times 10^9/L</math>. 
 
a) If the duration is less than or equal to 7 days, resume administration at the original dose level.
 
b) If the duration is greater than 7 days, resume HQP1351 administration at a reduced dose level.
 
 
 
 |
| Grade 4 ( $< 0.5 \times 10^9/L$ )                                                                                                                                 | 
 
1. Interrupt HQP1351 administration until toxicity resolves to <math>\geq 1.0 \times 10^9/L</math>.
 
2. Restart HQP1351 administration at a reduced dose level.
 
3. If Grade 4 toxicity recurs, interrupt HQP1351 administration until toxicity resolves to <math>\geq 1.0 \times 10^9/L</math>, and resume administration at a reduced dose level.
 
4. A maximum of two dose reductions is allowed.
 
                                                                                                                                                            |

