| Febrile neutropenia                                                                                                                                        |                                                                                                                                                                                                                                                                                                                                                                                                                                                                                                                                                                                                                                           |
| Grade 3: ANC $< 1.0 \times 10^9/L$ accompanied by single body temperature $> 38.3^\circ\text{C}$ or body temperature $\geq 38^\circ\text{C}$ for more than 1 hour | 
 
1. Interrupt HQP1351 administration until ANC recovers to <math>\geq 1.0 \times 10^9/L</math> and there is no fever.
 
2. Restart HQP1351 administration at a reduced dose level.
 
3. If febrile neutropenia recurs, stop HQP1351 administration.
 
                                                                                                                                                                                                                                                                                                                        |
| Grade 4: life-threatening, urgent intervention indicated                                                                                                          | Stop HQP1351 administration.                                                                                                                                                                                                                                                                                                                                                                                                                                                                                                                                                                                                              |

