### **6.1 Pre-treatment Drugs**

Information on all prior anticancer treatments (chemotherapy, radiotherapy, immunotherapy, biotherapy, etc.) received by the subject should be collected and recorded in the CRF.

Prophylactic medications should be avoided before Cycle 1. If an AE occurs in Cycle 1, prophylactic drugs may be administered in subsequent cycles.

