### **6.2 Concomitant Medications and Concomitant Therapies**

After the start of study treatment, at any time during the study and within 30 days after the last dose, all treatments received by the patient will be considered concomitant therapies. Any treatments for AEs related to the study treatment or unresolved AEs received by patients (including those who withdrew from study treatment) should also be considered as concomitant therapies. In addition to the prohibited therapies or medications, other drugs may be used at the investigator's discretion after discussion and approval by the investigator and the sponsor, but the type, dose, route of administration and treatment cycles should be recorded truthfully in the CRF.

Appropriate routine supportive treatment (including blood transfusions) can be given to subjects with clinical indications according to clinical practice standard.

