### **6.3 Prohibited Medications and Therapies**

Patients should be treated according to clinical indications meeting medical standards and at the investigator's discretion. However, the following concomitant medications and therapies are not allowed:

- Surgery;
- Other anti-cancer therapies, including but not limited to: chemotherapeutic agents, immunotherapy (such as vaccines), biological response modifiers, radiotherapy, and/or systemic hormone therapy.
- Immune support drugs, except for 4 weeks before the first planned dose of the investigational drug, a stable dose of corticosteroids may be used.
- Traditional Chinese medicine claimed to have anti-tumor activity;
- Other medications that should be prohibited at the investigator's discretion.

If the subject's clinical condition requires a prohibited medication or treatment, the investigational drug should be discontinued and the subject should withdraw from the trial.

[figure not shown]

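### Protocol 9.5 both prohibits colony-stimulating factors in Cycle 1 (item 3) and says they are used in Cycle 1 (item 4), and no other section says which governs

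*Protocol*

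**What the plan says.** Section 9.5 opens its list of supportive measures with a permission: "Subjects will be allowed to receive appropriate supportive measures as deemed necessary by the attending physician". Two neighbouring items in that list then deal with CSF in Cycle 1.

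- Item (3), anemia, covers transfusion and erythropoietin and ends: "Colony stimulating factor is prohibited in Cycle 1 of this study".
- Item (4), neutropenia, consists of one sentence: "The neutrophil colony stimulating factors, including G-CSF, PEG-G-CSF, or GM-CSF are used in Cycle 1 of the study".

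Dosing after neutropenia is set in 4.3.2, Table 2. For a recurrent Grade 3 event the original dose is resumed if the neutropenia lasted 7 days or less. Otherwise: "If the duration is greater than 7 days, resume HQP1351 administration at a reduced dose level". Section 4.3.1 allows at most 14 days of interruption. Beyond that the subject leaves the study, unless continuation at a low dose is agreed.

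**The concern.** The two items name the same class of drug and the same cycle, and they cannot both be followed. Item (4) is a complete sentence with no sign of a gap or redaction, and it sits in a list of allowed measures, so a site can fairly read it as permission. Another site can rely on item (3) and withhold the drug.

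What is at stake is consistent handling of a toxicity that the protocol plans for. Table 2 has rows for Grade 3, Grade 4 and febrile neutropenia, and section 1.5.2 lists decreased neutrophil count among the common events in CML patients. CSF can shorten neutropenia, so the same event could lead to different dose actions depending on which item the site followed.

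**Working it through.** This is a comparison of texts. The protocol gives no figure to reproduce.

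**Step 1: does item (3) apply only to anemia?** No. Its last sentence refers to the study as a whole, and CSF is not among the anemia treatments that the item lists. The conflict with item (4) remains.

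**Step 2: does any other section settle it?**

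| Section | What it covers | Does it settle CSF use in Cycle 1? |
|---|---|---|
| 3.1 | A baseline neutrophil count reached with CSF does not count for eligibility | No, it concerns entry only |
| 6.1 | Prophylaxis: "If an AE occurs in Cycle 1, prophylactic drugs may be administered in subsequent cycles" | No. It leans against prophylactic use in Cycle 1 but is silent on treating existing neutropenia |
| 6.2 | Other drugs at the investigator's "discretion after discussion and approval by the investigator and the sponsor"; routine supportive care by clinical standard | No. The first part calls for approval, the second permits, and neither names CSF |
| 6.3 | Prohibited therapies, including biological response modifiers | No. That entry stands under anti-cancer therapies, is not tied to Cycle 1 and does not name CSF |
| 4.3.2, Table 2 | Interruption and restart after neutropenia | No, it does not mention CSF |

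**Step 3: can the dosing limits fall where the rule is unclear?** Cycle 1 has 28 days, so D29 is C2D1. Dosing every second day from D1 falls on odd days. Blood counts after the first dose are scheduled on D8, D15 and D22. The 14-day limit can be counted from the last dose taken or from the first dose withheld. On nominal days, ignoring visit windows:

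- Neutropenia found on D8 (no dose that day): last dose D7, 7 + 14 = D21; first withheld dose D9, 9 + 14 = D23. Both lie inside Cycle 1.
- Neutropenia found on D15 before dosing: last dose D13, 13 + 14 = D27; first withheld dose D15, 15 + 14 = D29 = C2D1.
- Recurrent Grade 3 neutropenia found on D22: the 7-day cut is 22 + 7 = D29 = C2D1.

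So both limits can fall within Cycle 1 or right at its end. This shows that the ambiguity can meet a dosing decision. It does not show that it did so in any subject.

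**Step 4: how many subjects?** The protocol gives no rate of CSF use and no rate of severe or Cycle 1 neutropenia in GIST. Section 1.5.2 allows only a loose range for neutropenia of any grade in any cycle among the 36 GIST subjects:

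- If the list of hematological events at 20% or more is complete and correct as printed, decreased neutrophils are below 20%: 0.20 × 36 = 7.2, so at most 7 subjects.
- The list prints neutrophil count *increased* at 52.8%. If that direction were itself a slip, the figure would be 0.528 × 36 = 19 subjects.

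Only events that are severe enough to treat and fall in Cycle 1 matter here. That is some unknown part of either number.

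**The case against.** The strongest reply is that this is an editorial slip with an obvious reading. Item (3) is an explicit, study-wide prohibition. Item (4) is not worded as the neighbouring permissions are. Taken literally, it would tie CSF to Cycle 1 and say nothing about later cycles, which is odd. A lost *not* is the likeliest explanation. Sections 6.1 and 6.3 lean the same way, and the approval step in 6.2 would often catch a divergence. Labels and consent forms are in Chinese. If sites also work from a Chinese protocol (an assumption), they may never see this conflict.

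Most of this stands, and it is why the point is minor and why the fix follows item (3). It does not remove the error. The document does not show that a word was lost, and 6.2 also allows routine supportive care by clinical standard, so a site need not ask first.

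Some stronger readings are tempting but not supported:

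- *A subject who needs CSF in Cycle 1 must leave the trial.* Section 6.3 says that a subject whose condition "requires a prohibited medication or treatment, the investigational drug should be discontinued and the subject should withdraw from the trial". That sentence closes a list which does not name CSF, and nothing extends it to 9.5.
- *Dose-by-dose consequences at 30, 40 and 50 mg.* By the end of January 2021, 11 subjects had been enrolled at each of these doses, against about 10 planned. Section 10.1 foresees 10 to 20 further subjects in the non-randomized part, where adults receive 40 mg. Scenarios at 30 and 50 mg mostly describe groups already filled.
- *Distortion of a Cycle 1 dose-limiting toxicity window.* The current design states no such rule.

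**Conclusion.** The contradiction is real and can be confirmed from the text of 9.5 alone. It is a wrong instruction in a safety section, not a detail left for a later document. Its severity is minor.

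The practical consequence is possible inconsistency between sites in treating Cycle 1 neutropenia, with a knock-on effect on the 7-day and 14-day dosing limits. That rests on two assumptions: that sites work from this wording, and that CSF changes recovery time enough to cross a limit. The number of subjects is unknown and probably small.

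A reader might infer that the tolerability assessment or the recommended Phase II dose is undermined. The document does not support that. Under 4.4 the dose is chosen by the investigators and the sponsor on safety, tolerability, PK and available efficacy together, with no rule that turns on Cycle 1 neutropenia. Table 2 also applies whichever item governs.

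**What to change.** Take the CSF sentence out of item (3) and correct item (4) to read: *Neutrophil colony-stimulating factors (G-CSF, PEG-G-CSF, GM-CSF) are not to be used in Cycle 1.* This keeps the one explicit rule in the document and puts it under the toxicity it concerns.

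If the sponsor in fact intends to permit them, delete the sentence in item (3) and word item (4) as: *may be used in Cycle 1 if clinically indicated.*

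Separate rules for prophylactic and therapeutic use, or a withdrawal rule in 6.3, would be new design decisions and are not needed to remove the error.

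The cost is a wording correction in two adjacent items, with no new visits, tests, subjects or analyses.

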## **9.6 Overdose**

### **9.6.1 Definition of overdose**

It is unknown if there is a potential of abuse of HQP1351.

An overdose refers to an excessive dose of a drug that is taken intentionally or unintentionally. No specific information suggests that overdose of HQP1351 can be used during treatment. There is no specific antidote for HQP1351 overdose.

The pharmacological effects may also be persistent for a long time after serum levels of active HQP1351 are no longer present. It is unknown if dialysis is permitted for patients using HQP1351.

In case of overdose of HQP1351, stop use immediately and closely observe the subject for signs of toxicity. If clinically indicated, appropriate supportive care should be provided.

### **9.6.2 Reporting drug overdoses to the sponsor**

All overdose with or without an AE must be reported within 24 hours to the Sponsor.

## **9.7 Pregnancy**

The risks of HQP1351 use during pregnancy have not been assessed. Patients who may become pregnant or whose partners may become pregnant must use acceptable contraceptive methods. Female patients must have been more than 1 year after menopause or use an acceptable contraceptive method (barrier method in combination with spermicide, oral contraceptives, licensed contraceptive implants, injectable long-acting contraceptives, intrauterine devices, tubal ligation) during the study period and within 3 months after the EOT.

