9. Men and women of childbearing potential (postmenopausal women must be amenorrheic for at least 12 months to be considered of non-childbearing potential) and their partners are willing to take protocol-specified effective contraceptive measures from signing the informed consent form to at least 30 days after the last dose of the investigational product.

10. Able to understand and voluntarily sign the written ICF before any study-specific procedures.

11. Subjects must be willing and able to complete study procedures and follow-up examination.

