  9. Men and women of childbearing potential (postmenopausal women must be amenorrheic for at least 12 months to be considered of non-childbearing potential) and their partners are willing to take protocol-specified effective contraceptive measures from signing the informed consent from to at least 30 days after the last dose of the investigational product.
  10. Able to understand and voluntarily sign the written ICF before any study-specific procedures.
  11. Subjects must be willing and able to complete study procedures and follow-up examinations.

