#### **7.6 EOT Visit**

EOT visit should be performed within 14 days after the subject's last dose of HQP1351.

If a subject terminates treatment for the reason listed in section 3.3, the investigator should make the subject complete the EOT visit as far as possible and document the reason for treatment discontinuation in the subject's source documents.

[figure not shown]**During EOT visit, the following assessments must be completed:**

- Vital signs: blood pressure, pulse, respiratory rate and body temperature.
- Physical examination: A complete detailed physical examination will be performed.
- ECOG performance status
- Complete blood count with differential
- Serum chemistry
- Coagulation test
- Lipase and amylase
- Urinalysis
- 12-lead ECG
- Serum troponin I or T level
- Echocardiography
- Collection of samples related to exploratory biomarker.
- AEs
- Concomitant medications
- Tumor imaging assessment (if it is less than 4 weeks from the last imaging assessment, no repeat examination is required)

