### **9.7.1 Period of pregnancy information collection**

Any pregnancies that occur from the first dose of the study product to 30 days after the last dose will be reported in the appropriate form. If a pregnancy is determined more than 30 days after the last dose, the investigator may report it based on his/her clinical judgment.

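### For women of childbearing potential, inclusion criterion 9 and section 9.7 set different minimum contraception periods after treatment, from different anchors, and the duty to report a pregnancy in the gap is unclear

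*Protocol*

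**What the plan says.** Inclusion criterion 9 appears in the synopsis and again in section 3.1, and covers men and women of childbearing potential and their partners. The synopsis asks for "effective contraceptive measures from signing the informed consent form to at least 30 days after the last dose of the investigational product". Section 3.1 gives the same end point, "to at least 30 days after the last dose of the investigational product".

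Section 9.7 begins with a general duty that has no end date: "Patients who may become pregnant or whose partners may become pregnant must use acceptable contraceptive methods". It then turns to female patients. Unless they are more than a year past menopause, they must use one of the listed methods "during the study period and within 3 months after the EOT".

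On reporting, section 9.7.1 says "Any pregnancies that occur from the first dose of the study product to 30 days after the last dose will be reported". Its next sentence reads: "If a pregnancy is determined more than 30 days after the last dose, the investigator may report it based on his/her clinical judgment". Section 9.7.2 has the investigator submit a pregnancy form no later than 24 hours after hearing that a female patient has conceived during her participation. It names no last day for this duty.

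The link between the two anchors is in section 7.6: "EOT visit should be performed within 14 days after the subject's last dose of HQP1351".

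**The concern.** The same women are subject to two minimum periods that differ in length and in starting point. Criterion 9 counts from the last dose and section 9.7 counts from EOT. Criterion 9 also refers to contraceptive measures specified in the protocol, and the list of acceptable methods is in section 9.7. A site that follows the reference therefore reaches a section with a different duration, and nothing says which one to counsel or monitor.

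What is at stake is subject protection and the completeness of pregnancy data. Section 9.7 itself says that the risk of this drug in pregnancy has not been assessed, and section 9.7.2 classes some pregnancy outcomes, including birth defects, as serious adverse events. If sites apply different periods, or differ on whether a later pregnancy must be reported, the safety record will be uneven.

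**Working it through.** The plan states no figure to reproduce. The check sets the passages side by side and puts both periods on one clock, in days from the last dose.

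**Inputs**
- Criterion 9 (synopsis and section 3.1): minimum end at day 30.
- Section 9.7, female patients: 3 months after EOT.
- Section 7.6: EOT visit 0 to 14 days after the last dose.
- Assumption: 3 months is 90 to 92 days.
- Assumption: the study period named in section 9.7 ends no later than EOT. A longer reading would widen the gap.

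**Length of the gap**
- End of the 9.7 period = days from last dose to EOT + length of 3 months.
- Earliest: 0 + 90 = day 90. Latest: 14 + 92 = day 106.
- Gap between the two minimums = end of the 9.7 period − 30.
- Smallest: 90 − 30 = 60 days. Largest: 106 − 30 = 76 days.
- If EOT means the end of treatment itself and not the visit, the offset is 0 and the gap is 60 to 62 days (92 − 30 = 62).

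**Can both rules be met?**
- A woman who follows section 9.7 continues to day 90 or later, so she also meets criterion 9.
- A woman who commits only to day 30 meets criterion 9 and falls about 60 to 76 days short of section 9.7.

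**Reporting after day 30 and before the 9.7 period ends**
- Section 9.7.1 makes reporting mandatory to day 30 and discretionary after that.
- Section 9.7.2 makes it mandatory within 24 hours for a pregnancy during participation. Section 7.7.2.2 continues survival follow-up every 3 months, and section 3.3.2 treats follow-up as part of taking part. On that reading such a pregnancy must be reported.
- Section 9.7.2 can also be read more narrowly. It has the woman advised to stop study treatment at once, which fits someone still on the drug, and 9.7.1 is the section headed as setting the collection period.
- The serious-adverse-event rules do not settle it. Section 9.7.2 lists the reportable outcomes with no time limit, section 9.2.1 ends collection 30 days after the last dose, and section 9.4 and note 22 to the schedule of assessments deal only with later events thought to be related to the drug.

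**The case against.** The best defence is that criterion 9 sets a floor. Thirty days is a minimum, so both rules can be obeyed together, and section 9.7 can be read as the more specific requirement that criterion 9 points to. This is right as far as it goes: a reader might infer that the rules are incompatible, and they are not. But no passage says that section 9.7 governs, and the eligibility text still accepts a commitment that section 9.7 does not.

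Four other strong readings are tempting and are not supported:
- That pregnancy reporting stops at 30 days. The second sentence of 9.7.1 keeps it open at the investigator's discretion.
- That men face two conflicting periods. The 3-month period is stated for female patients only. For men, section 9.7 gives no end date, so it does not contradict criterion 9.
- That mandatory reporting must last at least as long as contraception. No passage requires this, and a shorter reporting window is not in itself a contradiction.
- That subjects have been told two different things. Consent pages are not available for this review, so what subjects are told cannot be checked.

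It is also fair to say that later pregnancies are not plainly outside collection. Sections 9.7.2 and 7.7.2.2 may cover some of them, so coverage is unclear and cannot be called absent.

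**Conclusion.** The point holds as an internal inconsistency in a subject-protection rule. For women of childbearing potential the two minimum contraception periods differ by about 60 to 76 days, given 3 months of 90 to 92 days and EOT taken as the visit in section 7.6. The figure is the distance between two minimums. It does not measure how long any woman will actually go without contraception. Within that interval the duty to report a pregnancy depends on whether section 9.7.1 or 9.7.2 is applied.

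The text needs correcting because the protocol describes the risk in pregnancy as not assessed and no other passage resolves the difference. Which duration is right is a clinical decision and is not judged here. The point has no bearing on sample size, error rates, endpoints or dose selection.

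**What to change.** Reconcile inclusion criterion 9, in both the synopsis and section 3.1, with section 9.7, so that one duration is stated from one anchor. If EOT is kept as the anchor, say whether it means the visit or the end of treatment.

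State how sections 9.7.1 and 9.7.2 apply to a pregnancy that arises after day 30 but within the contraception period, including whether participation in 9.7.2 extends to follow-up. The sponsor decides both the duration and the reporting window.

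The cost is protocol wording, with the consent form brought into line where needed. Reporting work grows slightly only if the sponsor chooses a longer mandatory window.
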